# VI Study settings

# Study population

1.1. The environment: The study will be carried out in Niakhar (Garenne M 1986; Garenne M 1990) (N 1428’ - W 1624’), a rural area of Central Senegal, which has appropriate conditions for such investigations. These resources are inherited from two randomised controlled trials (Samb, Aaby et al. 1993; Simondon, Yam et al. 1996) performed between 1987 and 1995. Niakhar comprises a set of 30 villages under demographic surveillance since 1983. Situated 115 km to the east of Dakar, the population comprises approximately 31 000 people living in 30 villages divided into hamlets with a total of 1 800 compounds. On average there are fourteen persons living in each compound. The site (230 square kilometres) is one of dry savannah with approximately 400-mm of rain recorded from June to September. This study area is typical of much of sub-Saharan Africa, as malaria is unstable, with transmission occurring mainly from September to November.

1.2. Demographic and epidemiological surveillance: The French Research for Development Institute (IRD web site www.ird.sn) has undertaken longitudinal follow-up of the population in Niakhar since 1983. From 1983 to 1986, field workers performed annual surveillance, during which demographic events and other epidemiological information were recorded. In 1987, in order to meet the needs of a trial of high titre measles vaccines, the system was changed to weekly home-visit of 1800 compounds.. Two supervisors controlled the quality of work done by twelve field workers. In the period 1997 – 2000, for financial reasons, this surveillance team was reduced to six field workers. Routine collections of data are now done quarterly

1.3. Malaria transmission and mortality in Niakhar: The level of malaria endemicity in Niakhar has been assessed by Vincent Robert who used three cross sectional studies conducted in February, June and November 1995 (Robert, Dieng et al. 1998). The maximal level of parasitaemia was observed in November, corresponding to the seasonal transmission peak which is also the end of rainy season. Among those 0-9 years of age, the asexual parasite rates of *Plasmodium falciparum* were 36% in February (mid-dry season), 33% in June (start of transmission season) and 79% in November (end of wet season).

In that study, entomological data showed transmission rates of ten infective bites per person per year, mainly acquired during the rainy season. Most severe cases of malaria are observed in November, particularly among children less than five years old. The latest assessments of resistance for chloroquine, amodiaquine and SP have shown respectively 44%, 16% and 7% of resistant parasites (Sokhna, Molez et al.). Surprisingly, chloroquine is still used as first-line treatment in most government facilities despite official instructions of using SP plus amodiaquine as first line. In this area, malaria mortality occurs mainly in children under 5 years of age. From 1984 to 1992, it fluctuated between 2.3 and 7.4 deaths per thousand per year with an average of 4.2 per thousand. After the emergence of chloroquine resistance, it increased to 16 per thousand per year, representing the cause of one out of four deaths in the one to four years old age group (Trape et al. 1998).

1.4. Heath cares systems in Niakhar: The site has three health centres, each of them headed by a qualified nurse. Consultations are provided daily from Monday to Friday. Pre-natal and EPI activities are normally run according to national policies. These health structures receive the assistance of an IRD physician at least one day a week.

1. Inclusion and Exclusion criteria

2.1. Inclusion criteria**.**

Eligible subjects will fulfil all of the following criteria:

Age between 1 to 6 years of age

Informed consent obtained from parents or legal guardians

Permanent resident of the study area without an intention to leave it in the coming six months

No current participation in another malaria study

2.2. Exclusion criteria

Reasons for exclusion will include any of the following:

Any conditions causing an inability to take or retain oral medication.

Any chronic illnesses or severe conditions such as tuberculosis, epilepsy, obvious mental retardation or failure to thrive.

Severe congenital diseases such as heart malformations

Intake of an anti-malarial other than chloroquine within the previous two weeks

Known allergy to any of the antimalarial drugs used in the trial.

1. Study design

We will use an open label randomised trial comparing the following regimens:

- Artesunate one day plus SP

- Artesunate given for three days plus SP

- Artesunate plus Amodiaquine both given for three days

- Lapdap for three days

One of these combinations will be randomly allocated to all participants and given three times in early September, early October and early November 2004.

1. Sample size calculations

The trial is powered as an ‘equivalence’ or ‘negative’ trial, with the outcome being the cumulative incidence of malaria, ie the proportion of children having at least one episode of malaria during the course of the study. AS3+SP is the comparator and is expected to have cumulative incidence of 20%, and we aim to show that this is no more than 30% in the other three arms. To allow for three comparisons — AS3+SP compared with each of the other three arms — we set the significance level to 5/3% (≈0.0167%), one-sided. With 80% power, we need 336 children per arm (Jones, Jarvis et al. 1996). We expect no more than 20% to be lost to follow-up, which raises this to 420 per arm, or 1680 in total.

For the secondary drug resistance endpoint, this implies 336×0.2=67 cases on AS3+SP. To be conservative, we assume the same number on the other arms (if they turn out to be less effective than AS3+SP, this will only increase the power for this secondary endpoint). Among these cases, based on our previous study, we expect the prevalence of *dhfr* mutations at codons 108, 59 and 51 to be 90% in the AS1+SP arm. The 67 cases per arm then give us 77% power to detect a difference of 20% (ie 70% prevalence) in the other arms, with a significance level of 5% (two-sided, (Fleiss 1981)).

1. Enrolment procedure and follow-up

The first step will be to hold by June 2004 several community-meeting with all the partners involved in the trial including the villagers. Then, eligible children will be included if they meet the inclusion criteria and if their parents or guardians provide informed consent. The explanation provided to parents will be given in local languages, emphasising the potential public health impact for malaria control of the study (*appendix 1*). When approval is obtained after a medical examination, a study number will be allocated immediately (*appendix 2*). In addition, an ID card will be given to all participants to facilitate identification at every contact, at home or in the health centres. At the time of each drug administration, a clinical examination and an interview of parents will be performed. Children will pass through four teams respectively for identification, clinical examination, blood sampling and anti malarial drug administrations. Those who are febrile at a time of intervention will be tested for malaria and given two days treatment with Coartem® . Haemoglobin levels and drugs resistance markers will be assessed during two cross-sectional surveys conducted at the time of the first drug administration (September 04), and one month after the third and last drug administration (December 04).

1. Randomisation and drug distribution

Individual randomisation is proposed and will be done approximately three weeks before the first sIPT administration planned for early September 2004. Children will be given active drugs according to their allocation group. The investigators who do the randomisation will also separate the regimens into jars, and make a note of the code. They will therefore not be blind, but all field staff and lab staff involved directly in making observation on study subjects or their samples will be blinded to study group.

Individual notice will be given to all participants approximately one week before any intervention. Drugs will be given at the health centres.. For young children, tablets will be crushed, mixed with water and administered. All participants will be under observation for 15 minutes after drugs are taken. In case of vomiting, the drug will be re-administrated.

1. Patient assessment procedures & clinical management

Participants will be surveyed during a period of four months, September to December, with regular home visits. Morbidity screening will be carried out weekly since less frequent surveillance has been shown to underestimate the number of cases substantially. All visits will be documented using a standard form (*appendix 3*). Two days treatment with Coartem®  will be given to cases of clinical malaria defined as children who are slide positive and who have a history of fever and or vomiting within the past twenty-four hours. (Rogier, Ly et al. 1999).

A consultation ticket (appendix 7) will also be handed to the child’s parent for free consultation at the nearest health centre where physical and parasitological examinations are immediately done. Children who have been treated for malaria will be revisited at least once a day until day 3 in order to see if the treatment is effective and the child has recovered well. If parasites are still present at day 3 treatment will be pursued using Quinine after confirmation that the previous treatment had been well taken and not vomited.

For the 28 days following any confirmed malaria attack, a child will not be considered at risk for determination of malaria incidence rates.

Because follow-up will be based on passive surveillance, it is intended to organize two cross sectional surveys (September and December). Asexual forms of parasites, gametocytes and packed-cells volume will be measured for every child.

An experienced supervisor employed by the IRD will control the performance of the field-workers by randomly re-visiting in the afternoon participants seen in the morning.

Treatment will be provided for free at the three main health centres in the study area.

1. Assessment of resistances to antimalarials

At the time of the cross-sectional surveys filter paper blood samples will be collected and stored at 4 o C prior to analysis of molecular markers for resistance. For those children parasite-positive by microscopy, DNA will be extracted from the filter paper samples using standard techniques and amplified using PCR (Djimde, Doumbo et al. 2001). The reaction products will be probed for defined mutations in the dihydofolate reductase (*dhfr*), dihydroptypteroate (*dhps*) (Peterson, Di Santi et al. 1991) and *pfcrt* genes of *Plasmodium falciparum* using SSOP (Alloueche, Silveira et al. 2000). The prevalence of *dhfr* and *dhps* mutations associated with resistance to pyrimethamine will be compared between pre and post sIPT treatment samples in children who receive SP plus artesunate or Lapdap. Children who receive amodiaquine plus artesunate will act as controls. Similarly changes in the prevalence of *pfcrt* mutations before and after treatment will be measured in children who receive sIPT with amodiaquine plus artesunate whilst samples from children who receive SP or Lapdap will act as controls

1. Assessments of adverse events

Adverse events will be defined as any signs or symptoms, which first develop or increase in severity within seven days after intake. Any serious adverse events such as death or admission to hospital which occur within one week of drug administration will be thoroughly investigated and reported within 24 hours to the DSMB. To determine the prevalence of minor side effects following drug administration such as headache, fever, weakness, abdominal pain, anorexia, nausea, vomiting, diarrhoea, rash, itching or sleep disorder 100 randomly selected participants in each treatment group will be visited at home seven days after each round of drug administration and a side effects questionnaire completed. (*appendix 5*) Field staffs who complete these questionnaires will be unaware of the treatment group to which the child belongs.

1. Participants withdrawal

Parents will be at liberty to withdraw their children from the study at any time for any reason; this decision will not prejudice their children receiving malaria treatment.

Parents and legal guardians will also be informed that, on medical grounds, the principal investigator may decide to withdraw the patient. Reason(s) for this withdraw will be noted in the patient record form. In this case as well, study subjects will keep on receiving all the advantages enjoyed by continuing participants.

11. Monitoring

Clinical monitoring will be done as decided by the Consortium. Basically, a Data and Safety Monitoring Board (DSMB) will be set up with the agreement of the London School of Hygiene and Tropical Medicine (LSHTM), the Dakar University (UCAD) and the National Malaria Control Programme (PNLP). Reports of all cases of death will be given to the DSMB.

The DSMB will review the trial protocol and Standard Operating Procedures (SOPs) before the trial commences and decide on the reporting procedure that it requires.

All serious adverse events that occur within seven days of drug administration will be reported to the DSMB.

12. Recruitment and training of staff

Before commencement of the study, three nurses, two field supervisors, two drivers, seven field workers, two-biologist technicians and two data entry clerks will be recruited. A logistician and an IT manager are also needed for the study. Additional staff may be engaged when needed.

A two-day workshop will be held in early August 2004. During this meeting, the principal investigator will explain the aim of the study. Tasks will be allocated with detailed explanations of expectations for each member of the group. A formal assessment of the impact of the workshop on the participant’s understanding of the study procedures will be held. Last but not least, a strong team spirit will be built up during this retreat.

Finally a one-week pilot study will be organised including organisation of drug distribution in the field.

13. Data management

The first step of the data processing will deal with the selection of the approximately 1680 children aged from 1 to 6 years needed for the study (20% future refusal or loss to follow-up taken into account). This will be done using the demographic database of Niakhar.

13.1. Design and organisation of the trial database.

Information will be collected from two sources:

►From the Niakhar demographic database

Identification information of each individual: identification number, surname, first name, date of birth, gender, residency, and identification of parent

►From the sIPT trial

Drug administration: date and place of event

Morbidity: date of examination, symptoms

Blood sampling: date, parasite prevalence

Anthropometrical measurements

All this information will be structured and organised in order to have homogenous collections of data. Required files will be created accordingly. This first sequence of the work will be accomplished after detailed discussion of the questionnaires that will be used to collect information.

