13.3 Measurements of study end-points and statistical analysis

In this study, sample size calculations are particularly done for the drug resistance end-point based on the 2002 study. Knowing that in the comparator group (AS1 + SP) the prevalence of genes with mutations markers of SP resistance increased from around 50% to 90%, the level of increase in the AS3 + SP could be looked at, with the assumption that it won’t be more than 50% to 70%.

The *dhfs*, *dhfr* and *pfcrt* genes from *Plasmodium falciparum* isolates taken on pre and post sIPT filter paper blood samples during the two cross sectional will be analysed by PCR-RFLP. Individual data will be tabulated according to the drugs regimen allocation.

The second end-point is an estimate of the effect of sIPT using the four regimens on the occurrence of the first or only clinical episode of malaria. The primary result is unadjusted protective efficacy, defined as (1-rate ratio). *Kaplan Meier Method* will be used to plot time-to-event analyses for first malaria attack after intervention, and *Log-rank* test to assess potential differences in the analyses.

Figure 2: Framework summarising the data management tasks

Back to the field

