**Main trial database**

The database will be used to extract analysis files and to produce on a monthly basis statistical information such as:

- Basic demographic analysis of study population followed during the month (age distribution, sex ratio, geographic distribution etc…)
- Number of those followed up, lost to follow-up, died, refused and withdrawn
- Number of samples before and after the interventions
- Number of children who have been completely followed during the month
- Number of child-days a risk[[1]](#footnote-2)1
- Number of first fever, or first clinical malaria attacks
- Total number of fevers
- Total number of clinical malaria attacks
- Proportion of children free from malaria since the start of the trial[[2]](#footnote-3)2
- Proportion of children free from malaria since the last intervention
- Proportion of urine tests positive for chloroquine metabolites
- Proportion of serious adverse events after drug administration

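### The 10-point non-inferiority limit is set on a raw proportion, and none of the planned methods that handle loss to follow-up is tied to it

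*Protocol*

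**What the plan says.** The sample size section (section VI, item 4) describes an equivalence-type trial whose outcome is "the proportion of children having at least one episode of malaria during the course of the study". It states that "AS3+SP is the comparator and is expected to have cumulative incidence of 20" per cent, and that "we aim to show that this is no more than 30% in the other three arms". The limit is therefore 10 percentage points on a difference of proportions. The error rate is fixed by "we set the significance level to 5/3% (≈0.0167%), one-sided", where the bracketed figure is evidently 0.0167 as a fraction, that is 1.67%. The size follows: "With 80% power, we need 336 children per arm", then "We expect no more than 20% to be lost to follow-up, which raises this to 420 per arm". The expected number of comparator cases is also worked out on 336 children, giving 67.

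Section 13.3 states the efficacy result differently. The primary result is one minus the rate ratio. The Kaplan-Meier method is "used to plot time-to-event analyses for first malaria attack after intervention", and a log-rank test assesses differences. The monthly outputs under the main trial database include child-days at risk, the numbers lost, and "Proportion of children free from malaria since the start of the trial". That last line carries a footnote mark, and footnote 2 again names Kaplan-Meier curves and the log-rank test.

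**The concern.** A child who leaves in October without an episode is neither a case nor a completed non-case. A raw proportion has no natural place for that child, and with up to 84 of 420 children per arm (20%) allowed for, the treatment of such children can move a comparison against a fixed 10-point limit. The methods in section 13.3 would deal with early loss, but they are attached to other quantities. A log-rank test asks whether the curves differ, and failing to find a difference does not show that the excess is below 10 points. A rate ratio has no 10-point limit and no fixed equivalent of one. So the protocol powers one quantity and analyses others, and the powered comparison is left without a named estimate that handles loss.

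At stake is some power on one reading of the text and some of the type I error on another, with the choice still open when the data are seen.

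**Working it through.** **Inputs from the sample size section:** comparator 20%, limit 30%, one-sided 5/3% = 1.667% (z = 2.128), power 80% (z = 0.842), 336 evaluable and 420 enrolled per arm, loss at most 20%.

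**Assumptions, not in the documents:** constant hazard over follow-up, and loss at a uniformly distributed time, unrelated to malaria risk.

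**1. The plan's own figures.** 336/0.8 = 420 and 4 × 420 = 1680, both exact. For 336 itself, with both arms truly at 20%, n = (z_alpha + z_power)² × 2 × 0.2 × 0.8 / 0.10².
- One-sided 1.667%: (2.128 + 0.842)² × 32 = 282.2, so 283.
- Tail area 0.833% (5/3% split over two sides): (2.394 + 0.842)² × 32 = 335.01, so 336.

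The stated 336 thus matches this formula only with the smaller tail. That is a separate matter; the calculations below use the stated one-sided 1.667%.

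**2. Why the rate ratio does not carry the limit.** Under constant hazard, 20% v 30% is a rate ratio of ln(0.7)/ln(0.8) = 0.357/0.223 = 1.60. If the comparator rate were 10%, the same 10 points (10% v 20%) would be 0.223/0.105 = 2.12. The limit has no single value on the ratio scale.

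**3. Lost children dropped (completers only).** Error at a true 20% v 30% stays nominal. Power with equal arms at 20% and 336 per arm is Φ(0.10/√(0.32/336) − 2.128) = Φ(3.240 − 2.128) = 86.7%.

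**4. Lost children counted as malaria-free.** With event probability p and λ = −ln(1 − p), a child lost at a uniform time has had an episode with probability 1 − p/λ. The share of episodes missed is then 48% at p = 0.20 and 47% at p = 0.30. The observed rate is p × (1 − share lost × share missed). The false pass rate is Φ((0.10 − observed difference)/SE − 2.128), with SE from 420 per arm.

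| Loss, comparator / test | Observed rates | Difference | SE | False pass rate |
|---|---|---|---|---|
| 20% / 20% | 18.1% v 27.2% | 9.1 points | 0.0287 | Φ(0.312 − 2.128) = 3.5% |
| 10% / 10% | 19.0% v 28.6% | 9.6 points | 0.0292 | Φ(0.153 − 2.128) = 2.4% |
| 10% / 20% | 19.0% v 27.2% | 8.1 points | 0.0290 | Φ(0.642 − 2.128) = 6.9% |

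**5. Simulation under the same assumptions,** 420 per arm, upper 98.33% bound on the difference:
- 20%/20% loss: malaria-free count 3.4-3.7%; completers only 1.7-1.8%; Kaplan-Meier difference with Greenwood error 1.5-1.8%.
- 10%/10% loss: malaria-free count about 2.2-2.6%.
- 10%/20% loss: malaria-free count about 6-7%; Kaplan-Meier 1.6-1.9%.
- Power, equal arms at 20% with 20% lost: Kaplan-Meier about 90%, completers only about 86-87%.

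**6. Dependence on the share missed.** With 20% lost in both arms, the normal approximation gives 2.5% if lost children miss a quarter of their episodes, 3.8% if half, and 8.1% if all. The rate doubles once share lost × share missed reaches about 8.5%: about 42% missed at 20% lost (0.085/0.20), or about 85% missed at 10% lost.

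**The case against.** The strongest reply is that the protocol does not count lost children as malaria-free. It removes them to get from 420 to 336, and it computes its 67 expected cases on 336. On that reading there is no inflation, and power is above the 80% target. This stands, and it is why the inflated error is a conditional risk and not the consequence of following the sample size section. An enrolment allowance is still not an analysis rule, and dropping lost children also discards episodes that were seen.

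A reader might infer that the protocol has no way of handling lost children. It does have censoring-based methods: the rate ratio with child-days at risk, the Kaplan-Meier curves, and the footnote linking those curves to the proportion free from malaria. What is missing is only the link from any of them to the 10-point limit.

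A reader might also infer that the error at least doubles. It does not: 20% is the stated maximum loss, about twofold is the result near that ceiling, and at 10% in both arms the multiple is about 1.3 to 1.6. Scenarios with 30% loss in one arm exceed the stated maximum and are not used here. The section on data management describes the 20% as covering refusal as well as loss, so not all of it need be follow-up that ends early.

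Finally, detailed loss handling often sits in a statistical analysis plan, and one may exist. That covers censoring dates and variance formulas. It does not cover the mismatch between the quantity powered and the analyses named, which is in the protocol text.

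**Conclusion.** The point holds in this limited form: the 20% v 30% comparison is defined on a raw proportion, and none of the analyses in section 13.3 tests it. On the reading the sample size arithmetic favours, the cost is about 3 to 4 points of power (about 86-87% against 90%), with error near nominal. If lost children were instead kept as malaria-free, the false non-inferiority rate would be about 3.5%, roughly twice the nominal 1.67%, at 20% loss in both arms; about 2.2-2.6% at 10%; and about 6-7% at 10% against 20%. All of these rest on constant hazard and uniform loss times. The documents give neither the pattern of loss nor the share of episodes that lost children would miss. The protocol places most transmission in September to November with a November peak; later episodes would mean that lost children miss more of them, so constant hazard is more likely to understate this effect than to overstate it. This is worth correcting, but it does not invalidate the design.

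**What to change.** In the sample size section and in section 13.3, define cumulative incidence as one minus the Kaplan-Meier estimate at the end of follow-up, in all randomised children. Keep any episode seen before loss, and censor other lost children at their last completed weekly visit. State that the 10-point limit is tested on the difference between these estimates, with its Greenwood standard error, at the stated one-sided level for each comparison with AS3+SP. The rate ratio, curves and log-rank test can stay as supporting results. Add one sensitivity analysis in which loss is related to malaria risk.

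The cost is wording only: weekly visits and Kaplan-Meier curves are already planned, and the sample size need not change for this. The small downside is reliance on censoring being unrelated to malaria risk, which the sensitivity analysis is there to examine.

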# V. Hypothesis

Three doses of artesunate combined with SP or amodiaquine, and Lapdap used alone will be equally as effective at preventing malaria in young Senegalese children when used for sIPT as a regimen of SP combined with one dose of artesunate and less likely to select for resistant parasites

Two major endpoints will be considered in this study (i) the incidence of clinical malaria in children receiving one of these four interventions, (ii) the prevalence of parasites carrying genotypes associated with resistance following sIPT at the end of the transmission season.

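### The efficacy hypothesis is set against AS1+SP but the sample size is powered against AS3+SP, and two sections disagree on which endpoint set the sample size

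*Protocol*

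**What the plan says.** Four arms are compared: AS1+SP, AS3+SP, AS+AQ and Lapdap.

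- **Section V, Hypothesis.** AS3+SP, AS+AQ and Lapdap will be equally effective "as a regimen of SP combined with one dose of artesunate and less likely to select for resistant parasites". AS1+SP is thus the reference for both efficacy and resistance. Two major endpoints follow, unranked, with malaria incidence listed first.
- **Section VI, Sample size calculations, first paragraph.** The outcome is the proportion of children with at least one malaria episode. "AS3+SP is the comparator and is expected to have cumulative incidence of 20" per cent, and "we aim to show that this is no more than 30% in the other three arms". The significance level is 5/3%, called one-sided, to allow for three comparisons: "AS3+SP compared with each of the other three arms". Power is 80%, which gives 336 per arm, 420 after 20% loss, and 1680 in total.
- **Same section, second paragraph.** Resistance is the secondary endpoint. The reference is AS1+SP at 90% mutation prevalence, against 70% in the other arms, with 67 cases per arm and 77% power.
- **Section 13.3.** "sample size calculations are particularly done for the drug resistance end-point based on the 2002 study". The text on resistance markers calls AS1+SP the comparator group. On malaria: "The second end-point is an estimate of the effect of sIPT using the four regimens" on the first or only clinical episode. The same paragraph then names unadjusted protective efficacy as the primary result.

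**The concern.** The trial has no placebo arm, so a claim of equal efficacy depends on the reference arm. The protocol's case for the trial starts from AS1+SP: it is the 2002 regimen, it cut clinical malaria by 86% against placebo, and the aim is to find regimens that match it while selecting less for resistance. It is also the only one of the four regimens for which the protocol reports placebo-controlled efficacy in seasonal IPT.

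If the margin and the error allocation are built around AS3+SP, the trial can meet its powered objective without having shown what its hypothesis states about efficacy.

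The second conflict concerns what the sample size was for. One section derives it from malaria incidence and treats resistance as secondary. The other says it was done particularly for resistance. A reader cannot tell from the protocol which endpoint leads.

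**Working it through.** **1. Reproduce the stated sample size.** Inputs from the sample size section: 20% in both arms, limit 30% (margin 30 − 20 = 10 points), 80% power, level 5/3%.

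Formula: n per arm = 2p(1 − p)(z_α + z_β)² / margin².

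- With 5/3% split over two sides (0.00833 per side): z_α = 2.394, z_β = 0.842, squared sum 10.469. n = 0.32 × 10.469 / 0.01 = 335.01, rounded up to **336**.
- With 5/3% on one side, as labelled: z_α = 2.128, squared sum 8.819. n = 0.32 × 8.819 / 0.01 = 282.2, rounded up to 283.
- 336 / 0.8 = 420, and 4 × 420 = 1680.
- Resistance: 336 × 0.2 = 67 cases. 90% v 70% at two-sided 5% with continuity correction gives 77.1%, matching the stated 77%.

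The malaria inputs produce the 336. The resistance power follows from it. So the sample size section's account of what set the sample size is the one the arithmetic supports. (The one-sided label against the two-sided match is a separate matter.)

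**2. List the efficacy pairs.**

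| Pair | In the hypothesis | Among the powered tests |
|---|---|---|
| AS+AQ v AS1+SP | yes | no |
| Lapdap v AS1+SP | yes | no |
| AS3+SP and AS1+SP | AS3+SP as good as AS1+SP | AS1+SP no more than 10 points worse than AS3+SP |
| AS+AQ v AS3+SP | no | yes |
| Lapdap v AS3+SP | no | yes |

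**3. Can the missing pairs be inferred?** In terms of incidence,

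Lapdap − AS1+SP = (Lapdap − AS3+SP) + (AS3+SP − AS1+SP).

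A successful powered test bounds the first term at 10 points. The one-sided test of AS1+SP against AS3+SP bounds AS1+SP − AS3+SP from above, so it puts no upper bound on the second term. If that pair were read as two-sided equivalence, the second term would be bounded at 10 points and the sum at 10 + 10 = 20, twice the margin. The same holds for AS+AQ.

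**4. Resistance.** Section V, the second paragraph of the sample size section and section 13.3 all take AS1+SP as the reference. There is no conflict.

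**5. Effect of making AS1+SP the efficacy reference.** The formula is symmetric, so at 20% and a 10-point margin n stays 336. The protocol gives no cumulative incidence for AS1+SP, so a range is assumed here, equal in both arms:

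| Assumed incidence | n for 80% power, 0.00833 per side | Power at 336, 0.00833 per side | Power at 336, one-sided 1.67% |
|---|---|---|---|
| 10% | 189 | 97.3% | 98.6% |
| 15% | 267 | 89.2% | 93.3% |
| 20% | 336 | 80.1% | 86.7% |
| 25% | 393 | 72.6% | 80.7% |
| 30% | 440 | 66.8% | 75.8% |

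**The case against.** **The reference may differ by endpoint.** Section 13.3 calls AS1+SP the comparator only when discussing resistance markers, in agreement with the rest of the protocol. That stands, and section 13.3 is not evidence of a second efficacy comparator. It does not remove the conflict, because the Hypothesis section applies AS1+SP to efficacy too.

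**AS3+SP may be the stricter benchmark.** The sample size section allows for the other arms being less effective than AS3+SP. If AS3+SP is truly no worse than AS1+SP, a regimen within 10 points of AS3+SP is also within 10 points of AS1+SP. That is sound, but it rests on a premise that the stated one-sided test does not establish.

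**The wording is equivalence.** Both sections speak of equal effect or equivalence, and 336 matches a two-sided split. On that reading the AS3+SP/AS1+SP pair is covered. This is fair. The stated test, however, is one-sided against an upper limit, and the other two pairs stay outside on either reading.

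**A stronger reading is tempting:** that the comparisons with AS1+SP will never be made, or that the lead endpoint is left open to be picked once results are known. The protocol does not support either. A sample size section fixes what is powered, not every analysis; the specific objective compares all four regimens, and section 13.3 plans survival curves and log-rank tests. The same section names protective efficacy as the primary result, and its reference to a second endpoint may mean only second in order of description.

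**Conclusion.** The point holds for efficacy. Of the three hypothesised pairs, two (AS+AQ and Lapdap v AS1+SP) are not among the powered comparisons, and the third is powered in the opposite direction under the stated one-sided test. A two-sided reading would recover that third pair but would leave the indirect bound on the other two at 20 points. How far this could mislead depends on the true difference between AS3+SP and AS1+SP, on which the protocol gives no incidence figures.

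The conflict over what set the sample size is also real, but narrower. It rests mainly on the sizing sentence in section 13.3, which contradicts the sample size section and the arithmetic. The sample sizes themselves reproduce; the fault is in what they are attached to.

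**What to change.** 1. Name one efficacy reference arm and use it in both the Hypothesis and the Sample size calculations. AS1+SP is preferable: it is the hypothesis's own reference and the only trial regimen with placebo-controlled seasonal IPT efficacy in the protocol (86%). The three powered comparisons then become AS3+SP, AS+AQ and Lapdap, each against AS1+SP. The alternative is to keep AS3+SP and restate the efficacy hypothesis against it.
2. If AS1+SP is chosen, state its assumed cumulative incidence. At 20% with the 10-point margin, 336 per arm is unchanged. If a higher rate is assumed, restate the power at 336 (72.6% at 25%, 66.8% at 30%, at 0.00833 per side) rather than enrol more children.
3. Correct section 13.3 to say that the sample size was set by the cumulative incidence of clinical malaria, the primary endpoint, and that resistance is secondary with 77% power. Leave AS1+SP as the resistance reference.

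The cost is rewording in three sections plus one stated assumption. Enrolment need not change; the price of a higher assumed incidence is a lower stated power.
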